### Outcomes

In this study, we will focus mainly on user experience, potential effects on health-related factors, and the use of COUCH during the implementation and follow-up phases. Furthermore, we will examine the demographics, applicability of the virtual coaches, and user’s interaction with the virtual coaches. Table 1 gives an overview of all the questionnaires that will be used during this study. All survey questions in the 3 questionnaires are listed in Multimedia Appendix 1.

**Table 1 table1:** Overview of the questionnaires and when they will be used.

		T0^a^	T1^b^	T2^c^
**User experience**				
	Technology Acceptance Model	–^d^	X	–
	System Usability Scale	–	X	–
	Willingness to pay	–	X	–
**Potential health effects**				
	EQ-5D-5L^e^	X	X	X
	Positive health dimensions	X	X	X
	Self-Management Ability Scale – short version	X	X	X
Demographics		X	–	–
**Applicability of the virtual coaches**				
	Rating scale	X	X	–
	Working Alliance Inventory	–	X	–

^a^Baseline.

^b^After the 4-week implementation phase.

^c^After the 4-week facultative follow-up phase.

^d^Not applicable.

^e^EQ-5D-5L: 5-level EQ-5D questionnaire.

#### User Experience

To determine the user experience, the Technology Acceptance Model [18,19] and System Usability Scale (SUS) [20] will be used. Furthermore, an exit interview will be conducted, and the willingness to pay will be measured. In this study, user experience domains will be used as external variables. In the literature, 4 constructs are found for the user experience of electronic health (eHealth) services. The first is enjoyment. van der Heijden [21] defined perceived enjoyment of a technology as the extent to which fun can be derived from using the system as such. He used 4 questions on a 7-point semantic differentials scale to measure the following 4 items: enjoyable – disgusting, exciting – dull, pleasant – unpleasant, and interesting – boring. The second construct is aesthetics. Lavie and Tractinsky [22] developed and validated a questionnaire to measure perceived website aesthetics. In this study, only classical aesthetics will be used. The third construct is control. In their study, van Velsen et al [23] used 3 control questions from Liu [24] that measure how users perceive the controllability of websites. The fourth construct is trust in technology. This domain is also a predictor for someone’s intention to use technology [23]. van Velsen et al [23] used 4 statements about trust in technology based on the study of Harrison McKnight et al [25] about the impact of consumer trust on intentions to transact with a website.

Perceived usefulness, perceived ease of use, and intention to use will also be used as constructs in this study’s questionnaire. The attitude toward the technology domain will be used as a demographic variable for the secondary outcomes. Both the perceived usefulness and perceived ease of use constructs are derived from Davis [18]. In his study, a new measurement scale for perceived usefulness and perceived ease of use was developed and validated. Both constructs are important when determining the intention to use: the less effort involved in a technology, the more it will be used, and the greater someone’s belief that using the technology would enhance his/her performance, the more it will be used [18,26]. Regarding the intention to use construct, van Velsen et al [23] based this construct on those of Davis et al [19] and Gefen et al [27] and expanded it with one item of their own. Based on the study by van Velsen et al [23], 3 statements were used in this study. Those 3 items were deemed the best to assess the intention to use.

The aesthetics, control, trust in technology, perceived usefulness, perceived ease of use, and intention to use constructs all use statements rated using a 7-point Likert scale, ranging from total disagreement to total agreement.

The SUS will be used to measure the usability of COUCH. Broekhuis et al [28] showed that the SUS is insufficient as a standalone tool for assessing the usability of eHealth technologies. However, another eHealth usability tool is not yet available [28]. The SUS consists of 10 statements with 5 response options that are rated using a 5-point Likert scale ranging from strongly disagree to strongly agree. The SUS score ranges from 0 (worst imaginable) to 100 (best imaginable) points [20].

Qualitative feedback from the participants will be obtained through a short semistructured exit interview at T1 (after interacting with COUCH for 4 weeks). During this interview, participants will be asked to share their ideas about COUCH. We will discuss the advantages, points for improvement, and problems experienced.

Willingness to pay will be measured by asking whether the participants are willing to pay for COUCH, and, if so, how many Euros they are willing to pay.

#### Potential Effect on Health-related Factors

Health effects will be measured through differences in scores within the EQ-5D-5L questionnaire, 6 domains of Positive Health, and Self-Management Ability Scale – short version (SMAS-S). The EQ-5D-5L questionnaire measures quality of life and consists of a descriptive system that includes 5 dimensions (mobility, self-care, usual activities, pain/discomfort, anxiety/depression) and a visual analogue scale. Each dimension has 5 levels, ranging from no problems to extreme problems. With the visual analogue scale, the participants rate their health on a vertical scale, labelled from the worst health you can imagine (0) to the best health you can imagine (100) [29].

Huber et al [30] studied how people think about health. They concluded that the concept of health no longer fits within the definition of the World Health Organization (health as complete wellbeing and absence of disease). The Institute for Positive Health created a tool to gain insight into the positive health of a person. This tool consists of 6 dimensions: bodily functions, mental wellbeing, meaningfulness, quality of life, participation, and daily functioning. Participants complete the questionnaire, resulting in a score between 0 and 10 for each dimension [30]. In our study, an adapted version will be used. Instead of completing a questionnaire consisting of 42 questions, the participants score each dimension from 0 to 10, as reported by van Velsen et al [31].

The SMAS-S is a questionnaire that measures 6 self-management abilities in older adults: taking initiative, investment behavior, variety, multifunctionality, self-efficacy, and positive frame of mind. It determines whether older adults need self-management courses [32].

#### Use of COUCH

The actual use will be determined using the platform’s log history. This outcome measure is defined as the frequency and duration of use overall, per week, and per session.

#### Demographics

Demographic data collected in the pretest questionnaire include gender, age, educational level, living situation, working status, attitude toward technology, self-reported level of physical activity, health literacy [33], and motivation level to live healthy. Attitude toward using technology and motivation level to live healthy will be explained in the following paragraphs.

To determine the participant’s attitude toward using technology, 4 items from Agarwal and Prasad [34] are included in the questionnaire. They developed and validated a new instrument consisting of 4 statements rated using a 7-point Likert scale, ranging from total disagreement to total agreement.

To get participants engaged in working on their health, it is important to determine their motivation to live healthy. With this information, the best suitable persuasive feature can be used in COUCH for each participant [31]. The motivation of an older adult to live healthy can be measured by a tool developed by van Velsen et al [31] based on the revised Sport Motivation Scale (SMS-II). The SMS-II was created and validated by Pelletier et al [35]. This questionnaire measures sport motivation using the Self-Determination Theory. The Self-Determination Theory distinguishes between 6 types of motivation: intrinsic motivation, extrinsic external regulation, extrinsic introjected regulation, extrinsic identified regulation, extrinsic integrated regulation, and a-motivation [36]. Those 6 types are included in the SMS-II tool. According to van Velsen et al [31], there are only 3 types of motivation in older adults to live healthy: intrinsic motivation, extrinsic external regulated, and a-motivation. They provided a set of 11 statements that will be used in our study. In our study, a fourth motivation type, dual motivation, will be included because some participants are not obviously intrinsically motivated nor externally motivated.

#### Applicability of the Virtual Coaches

The applicability of the virtual coaches will be measured using a rating scale and an adapted version of the Working Alliance Inventory Dutch version for use in the rehabilitation setting. This questionnaire will be completed for the 2 primary virtual coaches. This questionnaire measures how the patient feels about the therapeutic alliance: the better the therapeutic alliance, the more likely the patient will follow the treatment faithfully. Each participant will provide a score between 12 and 60: the higher the score, the more satisfied the participant is with the physical activity or nutrition coach and the more she/he trusts the coach [37].

### Sample Size

Because of the explorative character of this study, no sample size calculation was conducted beforehand. To answer the objectives of this study, the goal is to include 50 participants per country. So, in each round, 25 participants will be included per country. In our experience, participants are very enthusiastic to participate in this kind of evaluation with new technology before starting the study, but we expect that around 50% of the participants will drop out before the end of the implementation phase.

### Statistical Analysis

Statistical analyses will be performed using SPSS, version 19 for Windows (IBM Corp, Armonk, NY). For all analyses, the CIs will be set at 95%. Descriptive statistics, such as frequency, mean, SD, and percentages, will be used to describe demographics, user experience, actual use, and the applicability of the coaches.

The outcomes from the EQ-5D-5L, Positive Health questionnaire, and SMAS-S will be investigated using a mixed-model analysis for repeated measures to obtain the effect of using COUCH on the different measurements. The fixed factor will be the measurement time point (T0, T1, or T2). Post hoc comparisons will be conducted when required, and Sidak adjustments will be used to correct for multiple tests.

To assess the users’ interaction with the virtual coaches, the duration of the interaction (in seconds) and the number of dialogue steps with the coach will be used. With this analysis, we want to assess the effect of the conversation with the virtual coaches. To discover changes and possible trends, the duration of the interaction and number of dialogue steps will be analyzed for the two conditions. When the data follow a normal distribution, the outcome will be investigated using a paired *t* test; when the data are not normally distributed, a Wilcoxon signed-rank test will be performed.

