To properly evaluate the effectiveness of technology-supported health services, such as COUCH, in the real world is challenging [13-15], and it is currently increasingly acknowledged among experts that there is an urgent need for more pragmatic study designs to adequately evaluate technology-supported health services [13-16]. Microrandomization could be an appropriate alternative study design. The microrandomized trial was introduced by Klasnja et al [17] to overcome the limitations of current experimental methods, for instance randomized controlled trials, and to supplement the use of behavioral theory to guide the development of just-in-time adaptive interventions. As we are also interested in the effectiveness of the interaction between the user and the virtual coaches, we want to assess the applicability of the virtual coaches and the users’ duration of interaction with the virtual coaches of a fully working COUCH system implemented in a real-world setting among the target population. To assess the users’ interaction with the virtual coaches of COUCH, the interaction with one of the primary coaches (physical activity coach) will be microrandomized: Every time the user starts a conversation with this coach, the initiative of starting the conversation will be based on microrandomization. This microrandomization consists of the following two conditions: (1) The user takes the initiative and chooses the topic of the conversation, or (2) the system takes the initiative and automatically suggests the topic of conversation.

The predefined topics include gathering information about the user, goal setting, strategy selection, learning skills, and feedback and support.

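### The paired t or Wilcoxon test named for the microrandomised comparison cannot estimate the trends it is meant to find, and it is less efficient than a conversation-level model under most assumptions tried

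*Protocol article*

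**What the plan says.** The Trial Design section sets the unit of randomisation: "Every time the user starts a conversation with this coach, the initiative of starting the conversation will be based on microrandomization". The two conditions are user initiative, where the user picks the topic, and system initiative, where the system suggests one.

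The Statistical Analysis section names two outcomes for this comparison: "the duration of the interaction (in seconds) and the number of dialogue steps with the coach will be used". It gives the purpose as follows: "To discover changes and possible trends, the duration of the interaction and number of dialogue steps will be analyzed for the two conditions". It then fixes the test: "When the data follow a normal distribution, the outcome will be investigated using a paired" t test, and "when the data are not normally distributed, a Wilcoxon signed-rank test will be performed". It names no time term, no condition-by-time term and no participant effect for this comparison. The same section does use a repeated-measures mixed model for the three health questionnaires.

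On size, the Sample Size section says that "the goal is to include 50 participants per country", expects about half of the participants to drop out before the end of the implementation phase, and makes no sample size calculation.

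**The concern.** Each participant starts as many conversations as he or she likes over 4 to 8 weeks of use, and each start is randomised. The data are therefore a sequence of unequal length per person, with a random split between conditions. A paired test collapses that sequence to one difference per person and discards the order of the conversations, although order is what a trend is about.

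Time is likely to matter here. The Trial Design section says content is added to coaches during both rounds. The Limitations section says the follow-up phase brings no new content and that this may alter how often people interact.

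This is also the study's only randomised contrast, since everything else is an uncontrolled pretest-posttest comparison. If its analysis cannot address its stated aim, the microrandomisation yields less than it could. In addition, choosing between the two tests by a normality check changes what is being compared (a mean or a signed-rank quantity) according to the data.

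**Working it through.** **Inputs from the article.** Randomisation is per conversation, with two conditions and two outcomes. Planned size is 25 per round × 2 rounds = 50 per country, × 2 countries = 100. With about 50% dropout, about 50 complete the implementation phase. The article gives no power figure for this comparison, so there is none to reproduce.

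**Inputs assumed.** The article states neither the randomisation probability p nor the number of conversations per person. I take p = 1/2 and a two-sided 5% level, and vary the rest.

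**1. The trend question.** Let conversation j of person i have outcome y = α_i + β·a + γ·t + δ·a·t + error, where a is the condition and t is time or conversation number. The person's difference in condition means is

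D_i = β + γ(t̄_i1 − t̄_i0) + δ·t̄_i1 + error.

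If timing is balanced by randomisation, the γ term averages out and the mean of D_i estimates β + δ × (average time). That is one number for two unknowns. A constant effect, and an effect that starts at twice that size and fades to nothing, can give the same average. Neither test can separate them, whatever the assumptions.

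**2. Weighting.** Var(D_i) = τ² + σ²(1/n₁ + 1/n₀), where τ is the SD of the effect between people and σ = 1 is the SD within a person.

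| τ | 1 vs 1 conversation | 5 vs 5 conversations | Ratio |
|---|---|---|---|
| 0 | 2.00 | 0.40 | 5.0 |
| 0.25 | 2.0625 | 0.4625 | 4.5 |
| 1.0 | 3.00 | 1.40 | 2.1 |

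Both kinds of difference count once in the paired test.

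**3. Participants without a pair.** P(all k conversations in one condition) = p^k + (1−p)^k. At p = 1/2 this is 100%, 50%, 25%, 12.5% and 6.2% for k = 1 to 5, and 0.2% for k = 10.

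**4. Power, first assumed scenario.** 100 people; half stop after 1–4 conversations and the others have 4 + Poisson(6). Log-duration SD is 0.8 within and 0.4 between people. Duration falls 5% per conversation, and the true ratio is 1.22. About 24% of people have no pair.

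| Analysis | Constant effect | Effect SD 0.4 on log scale |
|---|---|---|
| Paired t, seconds | 44% | paired tests together: 51–59% |
| Wilcoxon, seconds | 57% | |
| Paired t, log seconds | 65% | |
| Conversation-level model with time term | 81% | 61% |

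Repeat runs of this scenario moved these figures by a few points (for example 43–48% for the paired t on seconds and 79–81% for the model). Much of the gap to the paired t on seconds comes from the log scale: 65 − 44 = 21 of 81 − 44 = 37 points.

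**5. Power, second assumed scenario.** Geometric conversation counts, effect 0.3 within-person SD, random-intercept model with robust standard errors.

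| N | Mean conversations | τ | Paired t | Model |
|---|---|---|---|---|
| 50 | 3 | 0.3 | 24% | 35% |
| 50 | 5 | 0.3 | 39% | 53% |
| 100 | 5 | 0.3 | 65% | 81% |
| 50 | 10 | 1.0 | 32% | 30% |

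**6. Validity.** With no effect in this second scenario, the paired t and Wilcoxon tests rejected in 4.5% to 5.0% of runs. The random-intercept model rejected in 5.2% to 7.3%. The highest figure came where the effect varied most between people and the model had no random slope.

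**The case against.** The strongest reply is that nothing here is invalid. The comparison is a secondary outcome in a study the article calls exploratory. A paired test on participant means holds its error rate, and giving each person equal weight is a reasonable target; weighting by conversations favours heavy users. How conversations are combined into a pair can be left to a fuller document. The Use of COUCH section also reports use per week and per session, so some time pattern will be visible. All of this stands, except that the time description is not by condition and so does not replace a trend analysis of the two conditions.

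Three stronger readings are tempting, and the documents do not support them.

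- A reader might infer that the paired test biases the result by dropping early leavers, and that a model would bring them back. A within-person comparison draws no condition information from someone who met only one condition, and a random-intercept model recovers only a little. The article's dropout figure also concerns leaving before week 4 of use, not having very few conversations.
- A reader might infer that picking a topic mechanically lengthens user-initiated conversations. The article does not say when timing or step counting starts, and who picks the topic is the intervention itself. Moving the start would redefine the outcome on a guess.
- A reader might infer that individual conversations will be paired and clustering ignored. The article does not say so.

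**Conclusion.** The mismatch is real and stated in the article: randomisation is per conversation, the aim is changes and trends, and the named tests reduce each person to one difference. That the trend question cannot be answered this way holds under any assumption.

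The efficiency loss is conditional. It rests on the assumed probability of 1/2, the assumed conversation counts and the assumed spread of the effect. It is substantial when the effect is similar across people and many have few conversations. It is small or absent, and can reverse, when the effect varies strongly between people. A large power gain should therefore not be claimed in general, and the results give no ground for calling the paired analysis biased. This should be fixed before analysis, but it does not undermine the study.

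**What to change.** Replace the t-or-Wilcoxon rule, including the normality check, with an analysis of every randomised conversation:

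- a linear mixed model or GEE clustered on participant for log(seconds), and a count model with the same structure for dialogue steps;
- fixed terms for condition, conversation number or week, and condition × time;
- a random slope for condition or robust standard errors, so that variation of the effect between people is allowed for.

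Keep the paired analysis of participant means as a sensitivity analysis that weights people equally.

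The cost is one rewritten paragraph and slightly more analysis work. The platform logs already supply the data. The trade-off is that heavy users carry more weight in the main estimate, which the sensitivity analysis will show.

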### Ethics and Informed Consent

This study will be conducted according to the principles of the Declaration of Helsinki (64th WMA General Assembly, Fortaleza, Brazil, October 2013) and in accordance with the Medical Research Involving Human Subjects Act (Dutch law: Wet medisch-wetenschappelijk onderzoek met mensen). According to this law, this study does not require formal medical ethical approval in the Netherlands. This has been checked by the CMO Arnhem-Nijmegen (file number: 2019-5555). Each participant will give his/her informed consent on paper. See Multimedia Appendix 2 for the informed consent form.

## Results

Recruitment of participants will take place twice. The first round of recruitment occurred from December 1, 2019 to January 30, 2020 in the Netherlands, during which time we recruited 26 participants. The first round of recruitment is still ongoing in Scotland. The second round of recruitment will occur from March 1, 2020 to April 30, 2020. For each round, we will recruit 25 participants per country. Participants are recruited through a mass mailing to older adults, snowball sampling, and advertisements in local newspapers and social media. Participants contact the principal investigator to sign up for participation. The principal investigator sends interested individuals an information letter via email and checks the inclusion and exclusion criteria. If a participant is eligible and still wants to be enrolled in the study, the first visit is planned by the principal investigator, and the study starts.

The first round of evaluation started on January 31, 2020. This round will last until April 15, 2020. The second round of evaluation will start in May 2020 and will last until July 2020. Figure 4 shows the planning of the evaluation. In August 2020, we plan to have the first results of this study.

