### Limitations

However, this study also has some limitations. First, there will likely be selection bias. Participants contact the researchers to enroll in the study. We expect that these participants are already more motivated to live healthy or already live more healthily than the average older adult population and the average adult population with type 2 diabetes or chronic pain. Second, the content that will be ready at the start of the evaluation only lasts for 4 weeks. During the follow-up phase, no new content will be provided to the participants. This can influence the interaction frequency during the follow-up phase. Finally, this study will possibly have to deal with confounders, for example if users receive advice from their health care professionals or others about a healthy lifestyle. This occurs in real life. To handle this as best as possible, confounders such as these will be discussed with the users during the exit interview.

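### The uncontrolled time-point contrast is read as the effect of COUCH, so any calendar change shared by all participants enters it; the round 2 wait could give a second pretest but is not used

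*Protocol article*

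**What the plan says.** Under Trial Design the study is an observational cohort with a pretest-posttest design, described as explorative. Under Statistical Analysis, EQ-5D-5L, Positive Health and SMAS-S are to be analysed "using a mixed-model analysis for repeated measures to obtain the effect of using COUCH on the different measurements", and the only fixed factor named is the time point (T0, T1 or T2). The abstract's Conclusions state that the results will decide for or against a hypothesis that includes positive health outcomes.

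Results gives the calendar. For round 1: "The first round of evaluation started on January 31, 2020. This round will last until April 15, 2020". For round 2: "The second round of recruitment will occur from March 1, 2020 to April 30, 2020", and "The second round of evaluation will start in May 2020 and will last until July 2020". Table 1 and the Participants section list questionnaires at T0, T1 and T2 only.

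Limitations mentions confounding, with outside lifestyle advice as its example, and says "confounders such as these will be discussed with the users during the exit interview". It names neither calendar change nor the lack of an untreated comparison.

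**The concern.** With no untreated group and time point as the only stated model term, study time and calendar time cannot be separated. A change that would have happened without COUCH is counted as a COUCH effect. Season is an obvious candidate because each round follows its own fixed stretch of the year, but any shared drift behaves the same way. An interview can bring out what differed for one person, such as advice from a clinician. It cannot isolate an influence that acted on everyone.

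What is at stake is the reading of a primary outcome: a significant T0-T1 change could be reported as support for the health hypothesis when COUCH did nothing. The schedule also leaves an opportunity unused, since round 2 recruits are enlisted and untreated for some weeks before T0.

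**Working it through.** **Sample size.** The plan's own figure reproduces: 2 rounds x 25 = 50 per country, and 2 countries give 100. The Sample Size section expects about 50% dropout before the end of implementation, which leaves about 50 at T1, or 25 per round. There is no power calculation to reproduce.

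**Timing.** T1 is 1 + 4 = 5 weeks (35 days) after T0, and T2 is 63 days after T0. For T2 to fall by April 15, round 1 T0 must lie between January 31 and February 12, so T1 lies between March 6 and March 18.

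**Whether season could matter.** Day length was computed from solar declination at assumed latitudes of 52 and 56 degrees N. From T0 to T1 it rises 2.2-2.7 h in round 1. In round 2 it rises 1.6-2.0 h for a May 1 start but only 0.3 h for a May 29 start. This shows that the calendar moves with study time, strongly in round 1 and weakly for late round 2 starts. It says nothing about the size or direction of any change in the scores.

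**False T0-T1 change under a pure shared shift.** Assumptions: COUCH has no effect; the shift is d SD; within-person correlation r is 0.5 or 0.7; n = 50; normal approximation to a paired change. SE = sqrt(2(1-r)/n), which is 0.141 for r = 0.5 and 0.110 for r = 0.7. The chance of significance is 1 - Phi(z - d/SE) + Phi(-z - d/SE), with z = 1.96 unadjusted. The Sidak level for three comparisons is 1 - 0.95^(1/3) = 0.017, giving z of about 2.39.

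| Shift d (assumed) | Unadjusted, r = 0.5 to 0.7 | Sidak for 3, r = 0.5 to 0.7 |
|---|---|---|
| 0.1 SD | 11% to 15% | 5% to 7% |
| 0.2 SD | 29% to 45% | 17% to 29% |
| 0.3 SD | 56% to 78% | 40% to 64% |

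**What the round 2 wait could supply.** Assume even sign-up over the 61 days from March 1 to April 30 and T0 on May 1. Those who sign up by April 10 wait at least 21 days: 41/61 = 67%, or about 33 of 50. The 95% half-width of their untreated change is 1.96 x sqrt(2(1-r)/33) = 0.34 SD (r = 0.5) or 0.26 SD (r = 0.7). For the T0-T1 change in 50 completers the same formula gives 0.28 or 0.21 SD, and in the 25 completers of one round 0.39 or 0.30 SD. The untreated change would thus be measured about as well as the change it is meant to inform.

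**How concurrent the wait is.** Round 2 sign-up opens on March 1. It overlaps round 1 T0-T1 by 5 days (T0 on January 31, T1 on March 6) to 17 days (T0 on February 12, T1 on March 18), out of 35. It covers all 28 days of round 1 T1-T2. A round 1 participant starting on March 11, which is possible because "The first round of recruitment is still ongoing in Scotland", would overlap fully, but T2 would then fall on May 13, after the stated end of the round.

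**Precision of a between-round difference.** With 25 round 1 completers and 33 waiting recruits, the half-width is 1.96 x sqrt(2(1-r)(1/25 + 1/33)) = 0.52 SD (r = 0.5) or 0.40 SD (r = 0.7).

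**The case against.** The best defence is that this is a known limit of a declared design. The article calls the study explorative, speaks of potential effects and makes no claim to power, and its list of confounders is given by way of example. That lowers the weight of the point but does not answer it, because the Statistical Analysis section and the abstract's Conclusions still attach a causal reading to the time contrast.

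A second objection is that nothing in the documents shows these scores to vary with season over five weeks, or in which direction. This stands. A reader might infer from the winter-to-spring dates that season pushes scores towards the hoped-for result. The documents do not support that, and the shifts in the table are assumptions.

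A third objection concerns the remedy. A reader might infer that the round 2 wait is a ready-made concurrent control for round 1 T0-T1. It is not. It overlaps only the last 5 to 17 of those 35 days and coincides mainly with the facultative phase. Round is set by recruitment date and not at random. All waiting recruits would be set against only the half of round 1 expected to remain. A half-width of 0.40-0.52 SD exceeds the largest shift considered. The between-round difference therefore cannot settle the question; the untreated within-person change is the useful quantity.

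**Conclusion.** The point holds in this form: the stated analysis attributes to COUCH a change over time that the design cannot separate from shared calendar change, the stated safeguard does not help, and an inexpensive second pretest is left unused. The dates and the absence of any questionnaire before T0 come directly from the article. The false-positive rates rest on assumed shifts of 0.1-0.3 SD, a correlation of 0.5-0.7 and 50 completers, and show what could happen, not what is expected. The count of about 33 recruits rests on even sign-up and a May 1 start.

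**What to change.** 1. For round 2, take consent at sign-up and have recruits complete EQ-5D-5L, the six Positive Health scores and SMAS-S then, online or on paper, and again at T0.
2. Report the untreated change from sign-up to T0 with a 95% CI beside the T0-T1 change, for recruits who waited at least 3 weeks. Present it as a partly concurrent, non-randomised second pretest. If a difference between rounds is shown, state the limited overlap and the comparison of all waiting recruits with completers.
3. Under Statistical Analysis, describe the result as change over time. Under Limitations, name calendar or seasonal change as a confounder that the exit interview cannot handle. The abstract's Conclusions should be read in the same terms.

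Cost: one short extra questionnaire for about 50 people, an earlier consent step (consent is on paper, so by post), and one more repeat administration in round 2 than in round 1, which should be acknowledged when rounds are pooled. No extra visits or participants are needed. Item 3 costs only wording and should be done even if items 1 and 2 are not.
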